#### Tests for interactions

Using appropriate interaction terms, we will test whether any effects of the intervention on teacher WEMWBS and PHQ-8 score differ according to: baseline teacher wellbeing/depression score (grouped as above or below the bottom quartile of the WEMWBS, or with a score of 10 or more on the PHQ-8), gender, geographical area (Wales/England) and school-level FSM. In the pilot less than 6 % of teachers selected an ethnicity other than white, and so ethnicity will not be considered in these analyses. We will look at the interaction between time and intervention, to test if the intervention had different effects at different time points. The effect of the intervention on student WEMWBS and SDQ score will be tested for interaction with baseline student wellbeing/SDQ score (grouped as above or below the bottom quartile of the WEMWBS and a score of 16 or more on the SDQ), gender, ethnicity, FSM eligibility, geographical area, and school level FSM. P-values will be interpreted with caution due to the low power and number of interactions being tested (e.g., we will use Bonferroni corrected or permutation *p*-values).

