		(range: 18.5–34.9)		(range: 16.1–25.1)	
	High	2 schools	2 schools	2 schools	2 schools
		(range: 39.2–77.0)		(range: 25.8–44.8)	

Notes

^a^Cut-offs for each FSM stratum were based on national mean and distribution, and therefore were slightly different for England and Wales (mean = 29.4 % over the past 6 years for England and 17.0 % over the past 3 years for Wales)

^b^Range given is the range of FSM among eligible schools in each strata

Many schools in England are Academies (state-funded but independent of local authority control), some of which are linked administratively in so-called academy chains. In order to avoid potential contamination at this administrative level, once one school from an academy chain has been selected, any others from the same chain and administrative level, will be excluded from the remaining selection process.

Selected schools will be screened to ensure the training package being used in the intervention (MHFA) has not previously been delivered within the school. Schools that are receiving or have received MHFA training will be excluded and replaced by another school randomly selected from the same stratum and geographical area.

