### Randomisation

Allocation will take place after baseline measures have been collected, and will be conducted by the study statistician, blinded to any identifying information. The statistician will randomly allocate schools stratified by geographical area and FSM scores (see Table 1) to intervention or control arm, using computer-generated random numbers.

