#### Secondary analyses

Analysis will include, linear (continuous outcomes), multinomial (ordinal outcomes) and logistic (binary outcomes) regression models depending on the outcome measure. They will be used to compare the outcome at follow up by arm, initially unadjusted for variables (accounting for clustering), then adjusted for baseline outcome and for school-level FSM and geographical area, as stratifying variables [41]. Then finally adjusted for important covariates such as age, gender and any other covariates that are not balanced at baseline.

For individual level outcomes that are measured at 12 and 24 months (e.g., PHQ-8), repeated measures models will be used, including a random effect for each individual, and random effects to allow for clustering by school. All individuals with at least one observation of the outcome measure will be included in the model for that outcome measure, under a Missing at Random (MAR) assumption.

For individual level outcomes that are only measured at 24 months (e.g., student WEMWBS), a regression will be used, with robust errors to account for clustering.

For school level outcomes that are measured at both 12 and 24 months (e.g., teacher absence), repeated measures models will be used. For outcomes at school level which are only measured at 24 months (e.g., student attainment), a simple regression will be used.

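### Moderation by baseline mental health is tested on dichotomised scores; the continuous score should be the main test, with the groups kept for display

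*Protocol article*

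**What the plan says.** The second of the protocol's secondary objectives asks whether effects differ by area, school FSM and individual characteristics, including baseline mental health. The section on tests for interactions sets the coding:

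- Baseline WEMWBS, for teachers and students, is "grouped as above or below the bottom quartile of the WEMWBS".
- Baseline PHQ-8 is split at 10 or more and student SDQ at 16 or more.
- The other teacher moderators are gender, "geographical area (Wales/England) and school-level FSM". The area contrast has two levels. No coding is given for school-level FSM.

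The outcome sections describe WEMWBS and SDQ as continuous variables. PHQ-8 is described as continuous, and also in ordinal and binary form with a cut at 10. The interaction section concedes low power and offers Bonferroni or permutation p-values.

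On FSM, a note to Table 1 says: "Cut-offs for each FSM stratum were based on national mean and distribution, and therefore were slightly different for England and Wales". The figures behind it are "mean = 29.4 % over the past 6 years for England and 17.0 % over the past 3 years for Wales".

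**The concern.** Splitting a continuous moderator in two treats everyone on one side of the cut as alike. A teacher just below the bottom quartile is pooled with the most distressed, and one just above it with the happiest. If the effect changes gradually with baseline wellbeing, much of the evidence for that change is discarded before the test is run.

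Baseline mental health is a named moderator in a stated research question. The tests have little power to begin with and will be corrected for multiplicity. An avoidable loss makes a null result harder to interpret: the trial could report no sign that the intervention works differently for teachers with poor wellbeing when the coding was too blunt to show it.

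This coding is fixed in the protocol text, so it is not simply a detail left to the SAP.

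**Working it through.** **The plan's own power figures.** No power is stated for any interaction, so only the main comparison can be reproduced. Inputs from the sample size section: difference 3, SD 8.4, 12 schools per arm, 50 teachers per school, coefficient of variation 0.5, 5% level (taken as two-sided).

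- Design effect at ICC 0.05: 1 + ((0.5² + 1) × 50 − 1) × 0.05 = 1 + 61.5 × 0.05 = 4.075.
- Standard error: 8.4 × √(2 × 4.075/600) = 0.979.
- Power from the noncentral t with 22 degrees of freedom: 83.4%, against 83% stated.
- At ICC 0.02: design effect 2.23, standard error 0.724, power 97.7%, against 98% stated.

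The main calculation is sound and is not in question.

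**Information kept by a bottom-quartile split.** Assume a standard normal baseline score and an effect that is linear in it. The information kept by a split at proportion q is the squared correlation between the score and the group indicator:

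efficiency = φ(z_q)² / (q(1 − q)).

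With q = 0.25, φ(z_q) = 0.318 and q(1 − q) = 0.1875. The efficiency is 0.539, a loss of about 46%.

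**Effect on power** (normal approximation, two-sided 5%, before any multiplicity correction):

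- 80% on the continuous score: (1.960 + 0.842) × √0.539 − 1.960 = 0.096, so power is Φ(0.096) ≈ 54%.
- 90% on the continuous score: (1.960 + 1.282) × √0.539 − 1.960 ≈ 0.42, so power is about 66%.

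**PHQ-8 and SDQ.** The documents give neither the shape of these distributions nor the share of this sample above each cut, so no figure is offered. If moderation is gradual, some information is lost in the same way.

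**FSM scale, for clarification only.** A school at 30% is at 30/29.4 = 1.02 times the English mean and 30/17.0 = 1.76 times the Welsh mean. In Table 1 it falls in the English medium stratum ("range: 18.5–34.9") and the Welsh high stratum ("range: 25.8–44.8"). A raw percentage therefore does not mean the same thing in the two nations.

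**The case against.** **In defence of the cuts.** A threshold is a reasonable choice if the question is about an identifiable group. The PHQ-8 cut at 10 is the protocol's own definition of depression, and effects in such groups are easy to communicate. The plan already urges caution, corrects its p-values and treats these analyses as secondary. The 54% depends on normality and linearity, neither of which is shown. The squared correlation is also symmetric: if the true effect were a step exactly at the quartile, the continuous test would be the one to keep only 54%. This justifies keeping the groups for display and checking for non-linearity. It does not make the split the better main test, because the protocol gives no reason to expect a step at the sample's bottom quartile.

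**Stronger readings that the text does not support.**

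- *A reader might infer that collapsing four areas to two is an error, or that adjustment will miss the randomised strata.* The Wales/England label belongs to the interaction contrast. The primary analysis adjusts for the stratification variables, the secondary analyses adjust for "school-level FSM and geographical area, as stratifying variables", and the randomisation section ("The statistician will randomly allocate schools stratified by geographical area and FSM scores") points to Table 1, which has four areas. The two-level contrast also fits the two-site rationale and the different trainers used in each country. It is the stronger test of a site difference: for 3 points at ICC 0.05, with twice the main standard error (1.96), power is 31% on 1 and 20 degrees of freedom, against 18% on 3 and 16 with four areas.
- *A reader might infer that raw FSM percentages will be pooled.* No coding is stated, and the nation-specific Table 1 level is a natural reading. Any estimate of how far English schools would dominate an FSM slope assumes raw percentages.
- *A reader might apply the normal-score formula to PHQ-8 using the 19.4% in the Background.* That share comes from PHQ-9 in the pilot, and nothing shows that PHQ-8 is normal.

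**Conclusion.** The point holds for the baseline-score moderators. Splitting scores that are collected as continuous is an inefficient choice fixed in the protocol. For WEMWBS the bottom-quartile split keeps about 54% of the information, so 80% power falls to about 54% and 90% to about 66%. These figures assume an approximately normal score and roughly linear moderation, at an uncorrected two-sided 5% level. For PHQ-8 and SDQ the argument applies in kind, without a number.

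The consequence is limited to the part of the second secondary question on baseline mental health. The primary comparison and its stated power are unaffected. The FSM scale is a matter for clarification only, and the Wales/England contrast is not at fault.

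**What to change.** - Make the interaction of treatment with the continuous baseline score the main moderation test for teacher WEMWBS and PHQ-8 and for student WEMWBS and SDQ.
- Add one simple check for non-linearity, such as a quadratic or spline term in the baseline score and its interaction with treatment.
- Report treatment effects with confidence intervals in the quartile and cut-point groups, labelled as descriptive.
- State that school-level FSM, where used as a moderator across both nations, enters as the nation-specific Table 1 level or as a value standardised within country.
- Keep Wales/England as the area interaction contrast.

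The cost is a few lines of wording and slightly more analysis on the same data. The main test then rests on linearity, which the second item addresses. The change should be made before outcome data by arm are seen.

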### Process evaluation

Informed by the Medical Research Council’s guidance [44], an embedded process evaluation will be conducted, using a combination of quantitative and qualitative methods. This will consider: mechanisms of change (see Fig. 1) and relevant contextual influences [45]; reach; contamination; intervention fidelity [46]; unintended harms [47]; acceptability; and sustainability.

Table 3 provides a summary of the ways in which the different process evaluation components will be assessed.

**Table 3 Tab3:** Process evaluation components and relevant data

Evaluation component	Relevant data
Mechanisms of change	*Teacher questionnaires* Stress at school Satisfaction at school Help provided to colleagues and students Help received from colleagues School’s attitude to staff and student wellbeing Quality of relationships in school *Student questionnaires* Help received from teachers School’s attitude to student wellbeing Quality of relationships with teachers *Interview with head teacher* Relevant new policies or practices introduced *Focus group with peer supporters* Nature of support provided *Focus groups with peer supporters and MHFA trainees* Learning from the MHFA training Application of learning Whether and how learning shared with colleagues *All focus groups (intervention)* Any perceived changes in school ethos or activities *Interview with peer support service users* Whether the service helped and how
Reach	*Teacher questionnaires* Use of the peer support service MHFA training completed *Termly peer supporter meetings* Record of how much help provided *Focus group with peer supporters* How service has been promoted *Focus group with students (intervention)* Perceptions of support from teachers and any changes
Contamination	*Focus group with teachers (control)* Any mental health training Any perceived changes in school ethos or activities *Focus group with students (control)* Perceptions of support from teachers and any changes *Audit of school activities* Any new activities in control schools similar to intervention
Intervention fidelity	*Focus groups with peer supporters and MHFA trainees* How much ALGEE model is used when supporting others Other MHFA techniques used when supporting others *Training observations* How well trainer sticks to core MHFA components *Interviews with trainers* Perceptions of MHFA core elements
Unintended harm	*Termly peer supporter meetings* Record of any harm experienced/observed by peer supporters *Focus group with MHFA trainees* Any negative experiences of attending the training
Acceptability	*Interviews with head teachers (intervention)* Views on peer support service and MHFA training *Focus groups and interviews with non-peer supporter teachers (intervention)* Views/experiences of the peer support service *Training observations* Reactions of trainees to the training *Interview with trainers* What went well or not well in the training
Sustainability	*Interviews with head teachers (intervention)* What is needed to make the peer support service sustainable Ways to embed the MHFA learning *Focus groups with peer supporters* What is needed to make the peer support service sustainable *Audit of school activities (intervention)* Any wider changes e.g., policies, processes *Interviews with funders* How well the intervention fits with local priorities What is needed for the intervention to be rolled out

The teacher and student surveys will contain questions that relate to mechanisms of change and reach:

#### Mechanisms of change

Participants will be asked to rate stress and satisfaction at work, help provided and received at school, school’s attitude to staff and student wellbeing, and quality of relationships in school in the questionnaires, using Likert scales. Logistic regression models will be used to examine differences by study arm at follow up, adjusted for baseline scores, school-level FSM and geographical area. We will examine whether baseline measures of these variables moderate the effect of the intervention by including the appropriate terms in the analysis model – however this is purely an exploratory analysis as power will be low, and there is always the potential for unmeasured confounding of the association between moderator/mediator and outcome. We will also examine the extent to which the MHFA training appears to have impacted on mental health, wellbeing and helping behaviour. We will use a Complier Average Causal Effect (CACE) approach (using Instrumental Variable analysis or Principal Stratification) [48] to compare those who completed the training in the intervention schools with those in the control schools who would have completed the training, had they been offered it (based on matching their gender, role in the school and years of experience with those who were trained).

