#### Secondary outcomes – teachers

Teacher depression, absence and presenteeism will be measured within the same self-report questionnaire. Depression will be measured using the 8 item Patient Health Questionnaire (PHQ-8) [5]. The PHQ-8 is suitable for measuring levels of depressive symptoms in population-based studies and is short enough to be used in self-report surveys. Unlike the 9-item version it does not contain a question about thoughts of self-harm – due to such a low number of participants in the pilot reporting suicidal thoughts, it was decided that measuring suicidality as an outcome was not necessary. Sickness absence and presenteeism during the last 4 weeks will be measured using questions adapted from the Work Productivity and Activity Impairment questionnaire (WPAI) [35]. Teacher absence days, retirement and resignations will also be measured at one and two years using routine data collected by schools.

Teacher PHQ-8 will be measured as continuous variable, and as an ordinal variable (a score of 0–4 indicating no depressive symptoms/5–10 indicating mild symptoms/10–14 indicating moderate symptoms/15–19 indicating moderately severe symptoms 20–24 indicating severe symptoms) and a binary variable, with a cut-point of 10 or more indicating depression [5]. Teacher absence and presenteeism will be treated as binary (any vs no absence in the previous four working weeks and health problems having 0 effect vs 1–10 effect on work over the previous four working weeks), and each variable will also be categorised and treated as ordinal, to examine whether the intervention has a differential effect on increasing levels of absence and presenteeism. Teacher absence, retirement/resignation and student attendance and attainment as reported by schools, will all be reported as a school level %.

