### Sample size calculation

The study is powered to detect a mean change of 3 points on the primary outcome - the WEMWBS score among teachers. This difference has been chosen as the minimum meaningful change discussed in a WEMWBS user guide [38]. A change of 3 points is also close to the difference in mean baseline scores between the highest and lowest ranked schools in the pilot study. Sample sizes were calculated using the clustersampsi command within Stata, which accounts for the clustered nature of the data by including intracluster correlation coefficients (ICCs) in the calculation. Based on the pilot data [34] we assumed a WEMWBS ICC of 0.01 (0.00, 0.05), a mean of 50 teachers followed up per school (with a coefficient of variation of sample size of 0.5), and a standard deviation for WEMWBS of 8.4. A sample size of 24 schools (12 intervention and 12 control) will achieve 83 % power at the 5 % significance level for an ICC of 0.05 (the highest of the confidence intervals in the pilot ICC); this would rise to 98 % for an ICC of 0.02.

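### The ordered Likert mechanism items are given a model that the protocol elsewhere reserves for binary outcomes, which implies an unstated cut and a loss of precision

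*Protocol article*

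**What the plan says.** The protocol article, under Process evaluation, Mechanisms of change, lists the questionnaire items meant to show how the intervention works: stress and satisfaction, help given and received, the school's stance on wellbeing, and "quality of relationships in school in the questionnaires, using Likert scales". It then sets the between-arm analysis: "Logistic regression models will be used to examine differences by study arm at follow up, adjusted for baseline scores", with further adjustment for FSM and area. It does not give the number of response categories, does not say whether the model is binary or ordinal, and names no cut.

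Two other sections show how the protocol uses these terms:

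- Secondary analyses, after linear models for continuous outcomes, lists "multinomial (ordinal outcomes) and logistic (binary outcomes) regression models depending on the outcome measure".
- Secondary outcomes – teachers gives absence and presenteeism an explicit binary split and adds that "each variable will also be categorised and treated as ordinal", so that effects at increasing levels can be seen.

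**The concern.** A Likert item is an ordered outcome. By the protocol's own labels, an ordered outcome goes to the multinomial model and a binary one to the logistic model, yet these items go to the logistic model. Read literally, each item would be split in two.

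That has two costs. Movement between categories on the same side of the cut no longer counts, so the arm comparison is less precise. The result also depends on where the cut falls. Absence and presenteeism are protected by a parallel ordinal analysis; the mechanism items are not.

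Whether the intervention works through its hypothesised mechanisms is a listed secondary research question. With an insensitive method, a null result could be read as a mechanism that did not operate.

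**Working it through.** **1. Reproduce the protocol's own power figure.** There is no power figure for the mechanism items. The figure for the primary outcome shows that the clustering inputs are understood. The trial is "powered to detect a mean change of 3 points on the primary outcome", with "a standard deviation for WEMWBS of 8.4" and "a mean of 50 teachers followed up per school (with a coefficient of variation of sample size of 0.5"), in 12 schools per arm. Two-sided 5% is assumed.

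- Design effect = 1 + ((CV² + 1)m − 1) × ICC.
- ICC 0.05: 1 + (1.25 × 50 − 1) × 0.05 = 4.075. Effective n per arm = 600/4.075 = 147.2. Power by noncentral t with 22 df = 83.4%, against 83% stated.
- ICC 0.02: design effect 2.23, effective n 269.1, power 97.7%, against 98% stated.

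Both figures reproduce.

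**2. Information kept by a binary cut, ignoring clustering.** Under proportional odds, the information per person about the log odds ratio is

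- ordinal model: I_ord = (1 − Σp_k³)/3, where p_k are the category shares;
- binary cut at cumulative share c: I_bin = c(1 − c).

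The loss is 1 − I_bin/I_ord. The category shares are not in the document, so two 5-point distributions are assumed:

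- Equal shares: Σp³ = 5 × 0.008 = 0.04, so I_ord = 0.96/3 = 0.320. Cut at 0.40: 0.24/0.32 = 0.75, loss 25%. Cut at 0.20: 0.16/0.32 = 0.50, loss 50%.
- Skewed shares (0.05, 0.10, 0.20, 0.40, 0.25): Σp³ = 0.08875, so I_ord = 0.30375. Cut at 0.35: 0.2275/0.30375 = 0.749, loss 25%. Cut at 0.15: 0.1275/0.30375 = 0.420, loss 58%.

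Other assumptions widen this range. A 4-point item with shares 0.1, 0.4, 0.4, 0.1 loses 14% at the median cut, and the skewed 5-point item loses 84% at its most extreme cut (0.05).

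**3. Add clustering by school.** Between-school variance adds equally to both models, so the relative loss shrinks:

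- loss = 1 − (τ² + 1/(m_eff·I_ord)) / (τ² + 1/(m_eff·I_bin));
- τ² = ICC/(1 − ICC) × π²/3, which is 0.0332, 0.0671 and 0.1732 at latent ICC 0.01, 0.02 and 0.05;
- m_eff = 50/(1 + 0.5²) = 40.

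Worked case, equal shares, cut 0.40, ICC 0.01: (0.0332 + 1/12.8)/(0.0332 + 1/9.6) = 0.1114/0.1374 = 0.81, loss 19%.

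| Assumed item and cut | No clustering | ICC 0.01 | ICC 0.02 | ICC 0.05 |
|---|---|---|---|---|
| Equal, cut 0.40 | 25.0% | 19.0% | 15.2% | 9.4% |
| Equal, cut 0.20 | 50.0% | 41.2% | 35.0% | 23.7% |
| Skewed, cut 0.35 | 25.1% | 19.3% | 15.6% | 9.7% |
| Skewed, cut 0.15 | 58.0% | 49.6% | 43.2% | 30.8% |

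The value 40 treats schools as about equally weighted. Weighting by teacher would use 50 × 1.25 = 62.5 and lower the losses somewhat. In the worked case, (0.0332 + 1/20)/(0.0332 + 1/15) = 0.833, a loss of 16.7% in place of 19.0%.

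**4. What this means for an interval.** A loss L widens the confidence interval for the log odds ratio by 1/√(1 − L). The smallest loss in the clustered columns (9.4%) gives 1/√0.906 = 1.05, and the largest (49.6%) gives 1/√0.504 = 1.41.

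**The case against.** The strongest reply is that proportional-odds regression is itself a form of logistic regression. The Mechanisms of change section does not say binary, and the labels come from a different section. In a condensed article, the exact form of the model and any cut may be left to a fuller document. Part of this stands: a missing cut-point alone would be no finding, and a reader who infers that the plan forces a dichotomy goes further than the text. What remains is that the protocol names a different model for ordinal outcomes, so binary is the natural reading of its own vocabulary.

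Three other strong readings are tempting and not supported:

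- *That a fixed share of information, such as a fifth to over half, is lost.* Such a figure needs the number of categories, their distribution and the cut, none of which is given. It also ignores clustering, which reduces the loss.
- *That these items are the only quantitative evidence on the logic model.* The same section plans a complier average causal effect analysis, and use of the peer support service is also surveyed.
- *That the protocol concedes low power for this comparison.* The remark "this is purely an exploratory analysis as power will be low" is about moderation by baseline measures, not explicitly about the arm comparison.

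It is also fair to say that the team does not discard order as a rule, as its handling of absence and presenteeism shows.

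**Conclusion.** The point holds as a mismatch between the named model and the stated scale, on the protocol's own usage. If the binary reading is right, precision is lost and the result depends on an unstated cut.

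In the clustered 5-point examples the loss is about 19–50% of the information at a latent ICC of 0.01, 15–43% at 0.02 and 9–31% at 0.05. These ranges rest on assumed category shares and cuts, on proportional odds being true, and on ICC values taken from the WEMWBS power calculation. They apply to teacher items at about 50 per school, not to student items, where clusters are larger. If the intervention acted mainly at one threshold, the loss would differ.

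The primary analysis of teacher WEMWBS as a continuous outcome is not touched. This is a cheap improvement to the answer on a secondary question, not a threat to the trial's main conclusion.

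**What to change.** In Mechanisms of change, state that each Likert item will be compared between arms by ordinal (proportional-odds) logistic regression with a school random effect, adjusted for the baseline item score, school-level FSM and area. The random effect also meets the general requirement, under Statistical analysis, to account for clustering. If a binary version is wanted, fix its cut in advance and report it only as a supplement to the ordinal result.

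The cost is a change of wording and of model command; the questionnaires already planned supply the data. The one real downside is that the proportional-odds assumption must be checked for each item.
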